### Safety

All adverse events during the study will be recorded at the 6- and 12-month follow-up, including severity, duration, and causality (i.e. relation to treatment). There is no anticipated harm and compensation for trial participation. The older adults will be offered treatment according to the standard dental care remuneration programme as a provision for post-trial care.

There will be no special criteria for discontinuing or modifying allocated interventions.

### Data analysis

Descriptive data will be presented using the mean and standard deviation (SD) or median and interquartile range for numeric variables, as appropriate. Categorical variables will be presented in numbers and percentages. The efficacy evaluation will be conducted according to intention-to-treat, including randomized subjects analysed by randomized treatment. Missing data will be imputed using multiple imputation. Drop-outs will be summarized descriptively by the treatment group with at breakdown of reasons for withdrawal.

Statistical analyses will be performed with appropriate methods for cluster RCTs using mixed effects models with DH as a random effect to account for intra-cluster correlations. Numeric variables will be adjusted for baseline values, if applicable. All questionnaire scales will be treated as numeric in this regard. Results will be presented using the mean difference between groups with 95% confidence intervals. The primary endpoints (change in ROAG and GOHAI from baseline to 12-month follow-up) will be tested at significance level *α* = 2.5%, a two-sided test, retaining the type I error rate of the primary endpoints at the 5% level. All other tests will be two-sided and conducted at the 5% significance level. No interim analyses will be conducted.

A total of 32 DH (16 per group) and 480 older adults (240 per group) will be included to demonstrate a clinically meaningful difference of 1 unit in ROAG at 80% power, adjusted for baseline values. The following assumptions were made: SD of change scores from baseline values = 3 since the older adults as a group are heterogeneous [45]. Weak to moderate correlation between baseline values and change scores = 0.3, m = 15 older adults per DH, a weak intraclass correlation coefficient within clusters = 0.05, significance level *α* = 0.025, two-sided test, and 25% drop-out [59]. A weak intraclass correlation coefficient is expected since DH is a licensed profession in Sweden, and ROAG is a validated instrument which shows little intraclass difference over time in nursing care [62]. A blinded evaluation of the SD, correlation, and intraclass coefficient will be conducted when 6-month follow-up data has been retrieved for 50% of the planned study participants, with a possibility for sample size adaption if judged necessary. Sample size calculations were conducted using SAS/STAT® Software, Version 9.4 of the SAS System for Windows (SAS Institute Inc. Cary, NC, USA).

In parallel, research will be conducted to describe the development of the interprofessional and interorganizational digital platform. Also, individual interviews are planned with professionals (DHs, NAs and managers), the dental team of the mobile unit (dentist and dental nurse) and older adults within the test and control groups. Further on, a health economic evaluation will be conducted.

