At baseline, six project coordinators (DHs) will collect informed consent forms from all participants, before the intervention. The six project coordinators will collect data and manage spontaneous reports of adverse events and other unintended effects of trial interventions. Empirical data will be collected. All older adults that participate will be enrolled in the dental care remuneration programme and in-home care. Participants within the test and control groups will answer on the following parameters at baseline, which will guide the evaluation.

At baseline:Empirical data (participant characteristics, i.e. sex and age).Mini mental state examination (MMSE-SR) [56].ROAG [50].GOHAI [54, 55].

*Primary outcomes* -* change from baseline to 12 months follow-up:*Older adults’ oral health status according to ROAG (50).Older adults’ self-perception of their oral health-related quality of life according to GOHAI [54, 55].

*Secondary outcomes*
SURE test [57] before and after health planning in oral assessments. The SURE test is based on four validated questions which describe the older adults’ uncertainty about which treatment to choose and aspects contributing to uncertainty about the benefits and risks of each option, what matters most to the older adults, support in making a choice and feeling sure about the best choice.Person-Centered Care Assessment Tool [58] to measure the professionals’ experience of the extent to which the care is experienced as being person-centred.All participants (DHs, NAs and older adults) will be measured by health-related quality of life according to EQ-5D-5L [59].OHAI [51], for measuring the ability to perform oral hygiene tasks. The OHAI should be used when indicated, when ROAG [50] shows 2 or 3 at the variables ‘teeth’ and ‘gum’, or if the older adult expresses concerns about difficulties with maintaining oral hygiene.

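### Naming baseline MMSE-SR, age and sex as covariates in the primary models would be a small, optional gain in precision; the analysis as written is valid

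*Protocol article*

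**What the plan says.** Under Phase VI (Evaluating outcomes), the baseline list contains "Empirical data (participant characteristics, i.e. sex and age", "Mini mental state examination (MMSE-SR) [56", ROAG and GOHAI. The sentence introducing the list says that these parameters will inform the evaluation, but not how.

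The Data analysis section specifies "mixed effects models with DH as a random effect to account for intra-cluster correlations". On covariates it says "Numeric variables will be adjusted for baseline values, if applicable". The sample-size paragraph speaks of "a clinically meaningful difference of 1 unit in ROAG at 80% power, adjusted for baseline values" and gives a correlation of 0.3 between baseline values and change scores. So the baseline value in question is that of the outcome itself.

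No other covariate is named for the primary models, and none is excluded. Multiple imputation is planned for missing data, without a list of the variables in the imputation model. MMSE-SR is not an eligibility criterion: older adults qualify by home care, registration in the remuneration programme, and not being under 65.

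**The concern.** Cognition is to be measured in all 480 older adults, with no cognitive restriction on entry, so the sample may span a wide range. It could plausibly relate to oral self-care (ROAG), to self-report (GOHAI) and to drop-out. That is clinical reasoning; the protocol gives no figure for it.

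On the protocol's own assumption the outcome's baseline explains little of the change score (a correlation of 0.3), so there is room for other covariates to help. With 16 dental hygienists (DHs) per arm, the arms may also differ by chance in the cognition or age of their older adults.

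The protocol states one adjustment rule, and that rule makes no use of three variables already collected. What is at stake is some precision, and how credible the point estimate looks if a baseline table shows imbalance. The validity of the test is not at stake.

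**Working it through.** **Inputs from the Data analysis section.** Difference 1 ROAG unit; "SD of change scores from baseline values = 3 since the older adults as a group are heterogeneous [45"; correlation of baseline with change 0.3; m = 15 per DH; ICC 0.05; two-sided alpha 0.025 per primary endpoint; power 80%; drop-out 25%; 240 older adults and 16 DHs per arm. After drop-out: 240 × 0.75 = 180 per arm and 15 × 0.75 = 11.25 per DH.

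**Assumption, not in the documents.** MMSE-SR, age and sex together explain a further fraction R² of the residual variance, taken as 0.02 to 0.10, with the ICC staying at 0.05.

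**Step 1: the plan's own figure.** n per arm = 2 × SD² × f × (2.241 + 0.842)² / 1² × design effect / 0.75, where f is the variance left after baseline adjustment. The design effect is 1 + (11.25 − 1) × 0.05 = 1.5125.

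- f = 1 − 0.3² = 0.91: 155.7 × 1.5125 = 235.5, and 235.5 / 0.75 = 314. With m = 15 the design effect is 1.70 and n is 353. Neither is 240.
- f = 1 − 0.3 = 0.70: 119.8 × 1.5125 = 181.1, and 181.1 / 0.75 = 241.5, close to the stated 240.

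The stated size therefore follows only if 0.3 is used as a proportion of variance. That is a separate matter, so both readings are carried forward.

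**Step 2: power with and without the extra covariates.** SE = √(2 × 9 × f × (1 − R²) × 1.5125 / 180) and power = Φ(1/SE − 2.241). For f = 0.91 and R² = 0, SE = 0.371 and power = Φ(0.454) = 67.5%.

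| Extra R² | SE (f = 0.91) | Power (f = 0.91) | SE (f = 0.70) | Power (f = 0.70) |
|---|---|---|---|---|
| 0 | 0.371 | 67.5% | 0.325 | 79.7% |
| 0.02 | 0.367 | 68.5% | 0.322 | 80.6% |
| 0.05 | 0.362 | 70.0% | 0.317 | 81.9% |
| 0.10 | 0.352 | 72.6% | 0.309 | 84.1% |

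A noncentral t with 30 degrees of freedom lowers the levels by about 4 points and leaves the gains much the same: 63.3% rises to 64.3–68.4%, and 75.9% to 76.8–80.5%, over R² of 0.02 to 0.10.

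**Step 3: chance imbalance.** Assume the covariate also has ICC 0.05. The standardized difference between arms then has SD √(2 × 1.5125 / 180) = 0.130, a 95% range of about ±0.25 SD. The matching shift in the ROAG estimate is 0.254 × √R² × 2.862, where 2.862 = 3 × √0.91. This gives about 0.10 units at R² = 0.02, 0.16 at 0.05 and 0.23 at 0.10, against a target of 1 unit. Over repeated randomizations this variation is already part of the mixed-model standard error.

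**The case against.** The strongest objection is that this is a preference and identifies no error. The adjustment sentence commits to one covariate and does not rule out more. Covariate lists and imputation variables commonly belong in the statistical analysis plan, which is not shown. The protocol does give the baseline measures some role in the evaluation. The prognostic strength used above is assumed, and the gain is small. All of this stands, and it is why the point is only an optional improvement to a rule that the protocol states.

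A reader might draw three stronger conclusions that the documents do not support:

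- **That the protocol excludes MMSE-SR, age and sex from the analysis.** It does not say so; it only leaves them unnamed.
- **That leaving them out makes the primary test unreliable with 32 clusters.** It does not. Under randomization the mixed model with a DH random effect allows for chance imbalance, and the outcome's own baseline is already adjusted for. What adjustment adds is a smaller standard error and less bias conditional on an observed imbalance.
- **That the 67.5% starting power results from the covariate choice.** It results from how the 0.3 correlation enters the sample-size formula. Under the other reading the start is 79.7%, and the extra covariates close little of the gap between the two.

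**Conclusion.** The point holds as a minor, optional improvement. The stated rule for the primary models uses only the outcome's own baseline, while three potentially useful covariates are already collected. Naming them would be worth about 1 to 5 points of power for ROAG at an assumed extra R² of 0.02 to 0.10, on either reading of the 0.3 correlation. It would also remove a conditional shift of roughly 0.10 to 0.23 ROAG units at the edge of the chance-imbalance range (f = 0.91).

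These figures rest on the protocol's SD, ICC and drop-out, on equal cluster sizes, and on an R² that no document supplies. At R² near zero the gain vanishes. The protocol gives no corresponding inputs for GOHAI, so no size can be put on that endpoint. Type I error is unaffected either way.

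**What to change.** Replace the adjustment sentence, as far as it concerns the primary endpoints, with: *Primary models adjust for the baseline value of the outcome, baseline MMSE-SR, age and sex as fixed effects.* Include the same variables in the multiple-imputation model, where they may also make the missing-at-random assumption more credible given the 25% drop-out expected. If an analysis plan already lists these covariates, a cross-reference is enough.

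The change is best made before recruitment, and at the latest before the planned blinded check of SD, correlation and ICC, because the relevant residual variance depends on the covariates. Added after unblinding, the covariates would look data-driven.

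The cost is one sentence and three fixed effects among 480 participants, with no new data collection. The small downsides are that missing MMSE-SR values would have to be imputed, and that there is little or no gain if the variables are not prognostic beyond the outcome's baseline.

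### The two primary endpoints are tested at 2.5% but reported with 95% confidence intervals, so a primary result can fail its test while its interval excludes zero

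*Protocol article*

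**What the plan says.** All the relevant statements stand in the Data analysis section of the protocol article.

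- Interval level, for results in general: "Results will be presented using the mean difference between groups with 95% confidence intervals".
- Primary tests: there are two endpoints, given as "change in ROAG and GOHAI from baseline to 12-month follow-up", and the level set for each of them is "2.5%, a two-sided test, retaining the type I error rate of the primary endpoints at the 5% level".
- Everything else: "All other tests will be two-sided and conducted at the 5% significance level".
- Sample size: "A total of 32 DH (16 per group) and 480 older adults (240 per group) will be included", aimed at a "clinically meaningful difference of 1 unit in ROAG at 80% power" and calculated at the same α of 0.025.

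The section describes no step-down and no passing of unused α from one primary endpoint to the other, so the multiplicity procedure is a plain Bonferroni split. It gives no effect size or power for GOHAI.

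**The concern.** A two-sided test at level α corresponds to an interval at level 1 − α. The 95% interval therefore matches every test in the plan except the two that decide the trial. For those two, the printed interval belongs to a 5% test that the plan deliberately does not use.

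Two consequences follow. A primary endpoint with p between 0.025 and 0.05 would be declared not significant beside an interval that excludes zero, and many readers would take that as success. Also, the multiplicity protection built into the tests does not carry over to the intervals: the two 95% intervals together do not cover both true differences with 95% confidence.

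**Working it through.** **The plan's own figure.** Two tests at 2.5% give a familywise error of at most 0.025 + 0.025 = 5%. If the endpoints were independent it would be 1 − 0.975² = 4.94%. The claim of 5% control is reproduced.

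**Inputs** (all from Data analysis): SD of change 3; correlation of baseline with change 0.3; 15 older adults per dental hygienist; intraclass correlation 0.05; 240 per group in 16 clusters; 25% drop-out; difference of 1 ROAG unit; α 0.025 two-sided.

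**Standard error for ROAG**
- Baseline-adjusted SD: 3 × √(1 − 0.3²) = 2.862.
- Completers: 240 × 0.75 = 180 per group, or 15 × 0.75 = 11.25 per cluster.
- Design effect: 1 + (11.25 − 1) × 0.05 = 1.5125.
- SE = 2.862 × √(2 × 1.5125 / 180) = 0.371.

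**Where test and interval disagree.** Normal critical values are 1.960 (5%) and 2.241 (2.5%).
- The 95% interval excludes zero from 1.960 × 0.371 = 0.73 units.
- The 2.5% test rejects from 2.241 × 0.371 = 0.83 units.
- With t critical values on 30 degrees of freedom (2.042 and 2.360) the zone is 0.76 to 0.88 units. It moves but does not vanish.

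**Chance of landing in the zone**

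| Situation | Excludes zero at 95% | Significant at 2.5% | Disagreement |
|---|---|---|---|
| No effect (either endpoint) | 5.0% | 2.5% | 2.5% |
| True power 80% (mean of Z = 2.241 + 0.842 = 3.083) | 86.9% | 80.0% | 6.9% |
| Stated inputs, 1-unit effect (mean of Z = 1/0.371 = 2.695) | 76.9% | 67.5% | 9.4% |

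The second row takes the stated 80% power at face value. The third uses the power that the stated inputs give under the calculation above.

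**Joint behaviour of the two 95% intervals.** Joint coverage is at least 90%, and 0.95² = 90.25% if the endpoints are independent. A reader who judged by exclusion of zero would face a familywise error of up to 10% (9.75% under independence), not 5%. Two 97.5% intervals have joint coverage of at least 95%.

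**Width of the matching interval.** 2.241 / 1.960 = 1.14, so about 14% wider.

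**Holm's procedure, as an option.** Holm adds a ROAG rejection only when ROAG has p between 0.025 and 0.05 and GOHAI has p ≤ 0.025. At zero correlation the gain is the product of the two chances. The GOHAI effect and the correlation between endpoints are assumptions, since the document gives neither.
- GOHAI has no effect: 9.4% × 2.5% = 0.2 points (6.9% × 2.5% = 0.2 points at 80% power).
- GOHAI at about half the effect (mean of Z 1.5): 1.0 to 2.1 points, by simulation with correlation 0 and 0.3.
- GOHAI effect equal in standardised terms: 9.4% × 67.5% = 6.3 points (6.9% × 80% = 5.5 points at 80% power). Simulation with correlation up to 0.5 keeps the gain at about 5 to 6 points.
- The chance of winning at least one endpoint is the same under both procedures, for example 96.0% under each with equal effects, 80% power and zero correlation.

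**The case against.** The strongest reply is that no inference is invalid. The decision rule is explicit, the sample size uses the same α, and nothing in the section lets an interval override a test. The sentence on 95% intervals can be read as a general presentation default, and unadjusted intervals beside adjusted tests are common. This stands as far as it goes: a reader might infer that the trial's type I error is inflated, and the document does not support that. The 10% figure arises only if someone uses the intervals as the test.

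A second reply is that interval levels are detail for a statistical analysis plan that is not shown. This does not remove the point. The article does not leave the level open; it fixes both levels, in adjacent sentences, and they do not correspond.

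A third tempting reading is that the fixed 2.5%/2.5% split is itself a mistake because Holm is never less powerful. The document does not support this either. Bonferroni is valid, prespecified and delivers the control that the plan claims. It also has simple matching intervals, which Holm's second step lacks. The gain from Holm depends on a GOHAI effect that is not stated and can be close to nothing.

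Finally, the 9.4% rests on a power of about 67.5%, not the stated 80%. That gap is a separate question about the sample size. At the stated 80% the figure is 6.9%, and the mismatch exists either way.

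**Conclusion.** The mismatch is real and confined to the reported intervals of the two primary endpoints. The tests and the 5% familywise control are sound. Its size is modest: a disagreement between test and interval in 2.5% of trials per endpoint under no effect, and in 6.9% to 9.4% for ROAG at the planned 1-unit effect, depending on whether the stated 80% power or the power from the stated inputs applies. The 0.73 to 0.83 unit zone rests on SE 0.371 and normal critical values. The harm is misreading of a borderline primary result, not a wrong decision rule.

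**What to change.** Amend the interval sentence in Data analysis so that the 12-month changes in ROAG and GOHAI are reported with 97.5% confidence intervals, matching their 2.5% tests, and all other outcomes keep 95% intervals. The cost is one sentence and primary intervals about 14% wider. Sample size, α and data collection are unaffected. The change is best made before recruitment, which the Trial status section plans for September 2025, so that the interval level is not chosen with a p-value in view.

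Optionally, replace the fixed split by Holm: test the smaller p at 2.5% and, if it is significant, the other at 5%. If this is adopted, the plan must state that an endpoint won only at the second step (p between 0.025 and 0.05) will always have a 97.5% interval that includes zero, and that the Holm test decides. If exact agreement of test and interval matters more than the possible gain in power, keep Bonferroni with 97.5% intervals.

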**Fig. 3 Fig3:**
[figure not shown]
Schedule of enrolment, interventions, and assessments within the intervention

In pairs, DHs within public dental care organizations in West Sweden will be randomized into test and control groups. Due to potential geographical specificities, NAs within the same municipality as the test control DHs will be asked to participate. As such, the test group will consist of 16 DHs and 16 NAs. They will form teams of two, and each team will collaborate with 15 older adults to conduct oral assessments and health care planning in home settings. The control group will consist of 16 DHs where each DH will perform oral assessments according to the dental care remuneration programme – that is, they will conduct business as usual on 15 older adults each. It is not mandatory but recommended for NAs to participate in the oral assessments; therefore, the number of participating NAs within the control group is unknown. Inclusion criteria for the older adults are having home care and being registered for the dental care remuneration programme. Inclusion criteria for the DHs are that they (in addition to their clinical work in public dentistry) perform oral assessments within the dental care remuneration programme, and for the NAs to work in-home care. *Exclusion criteria* for older adults is to be younger than 65 years old. In total, 480 oral assessments and health care planning sessions will be performed within the RCT including 480 older adults, 32 DHs and 16 NAs (+ unknown number of NAs in the control group) (Fig. 2).

The test group will participate in a two-day course, where initially an informed consent form will be signed by all participants, thereafter they will practise:Oral assessments according to ROAG [50].Oral hygiene ability assessments according to OHAI [51].Oral health-related quality of life assessment with the GOHAI [54, 55].Shared decision-making according to ODSF [52].Using the digital platform.

The course will be both theoretical and practical with elements of reflection. Also, test group management within dental and municipal healthcare will participate in a common half-day course where they will learn about the intervention and the digital platform. A dialogue regarding obstacles and opportunities will facilitate a common understanding and the continued implementation process. They will also set common goals regarding how to support the intervention.

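### The listed assumptions do not give 80% power for 1 ROAG unit with 16 dental hygienists and 240 older adults per group; they give about 67% by normal approximation

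*Protocol article*

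**What the plan says.** The Data analysis section of the protocol article (Phase VI) fixes the size: "A total of 32 DH (16 per group) and 480 older adults (240 per group) will be included to demonstrate a clinically meaningful difference". The target is a "difference of 1 unit in ROAG at 80% power, adjusted for baseline values". The inputs follow in the same paragraph: "SD of change scores from baseline values = 3"; "Weak to moderate correlation between baseline values and change scores = 0.3"; "m = 15 older adults per DH"; an ICC of 0.05; two-sided alpha 0.025; and 25% drop-out. Alpha is halved because ROAG and GOHAI are both primary endpoints.

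The design description under Phase VI confirms that 480 is the number enrolled and assessed at the start, 32 DHs times 15: "In total, 480 oral assessments and health care planning sessions will be performed within the RCT". Drop-out therefore comes off 480.

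The analysis is a mixed model with DH as random effect, adjusted for baseline. A blinded look at the SD, the correlation and the ICC is planned once half of the planned participants have 6-month data, and the sample size may then be adapted if that is judged necessary.

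**The concern.** The paragraph prints a full set of inputs beside a result, so the result can be checked without outside figures. A correlation of 0.3 between baseline and change removes only 0.3² = 9% of the variance. That is a small gain to set against a design effect of at least 1.5, a halved alpha and the loss of a quarter of the participants.

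ROAG is the only endpoint with a power statement. If the printed 80% is too high, the chance of missing the difference that the plan calls clinically meaningful is about one in three rather than one in five. Anyone planning from the paragraph, or later judging whether the sample size should be adapted, would be working from a calculation that its own inputs do not support.

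**Working it through.** **Inputs**, all from the Data analysis section: difference 1; SD of change 3; correlation r = 0.3; 15 enrolled per DH; 16 DHs and 240 older adults per group; ICC 0.05; two-sided alpha 0.025 (z = 2.2414); 80% power (z = 0.8416); 25% drop-out. After drop-out, 240 × 0.75 = 180 remain per group, or 15 × 0.75 = 11.25 per DH.

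**Attempt to reproduce the stated size**

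1. Residual variance after baseline adjustment: 9 × (1 − 0.3²) = 8.19.
2. Unclustered n per group: 2 × 8.19 × (2.2414 + 0.8416)² / 1² = 155.7.
3. Design effect at 11.25 completers per DH: 1 + 10.25 × 0.05 = 1.5125.
4. Completers needed per group: 155.7 × 1.5125 = 235.5.
5. Enrolled per group: 235.5 / 0.75 = 314, which is 20.9 or 21 DHs. The plan has 240 and 16.

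With t on cluster-level degrees of freedom (2k − 2 for k DHs per group), 22 DHs per group give 79.5% and 23 give 81.5%.

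**Power of the stated design**

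- Effective n per group: 180 / 1.5125 = 119.0.
- SE = √(2 × 8.19 / 119.0) = 0.371, and 1 / 0.371 = 2.695.
- Normal: Φ(2.695 − 2.2414) = Φ(0.454) = 67.5%.
- Noncentral t on 32 − 2 = 30 df: 63.3%.
- Difference detectable with 80% power: 0.371 × 3.083 = 1.14 units (normal), 1.19 (t).

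**Other readings of the same inputs**

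| Reading | Design effect | Analysed per group | Power, normal | Power, t (30 df) |
|---|---|---|---|---|
| Drop-out reduces n and cluster size | 1.5125 | 180 | 67.5% | 63.3% |
| Drop-out reduces n only | 1.70 | 180 | 61.8% | 57.7% |
| No drop-out at all | 1.70 | 240 | 75.6% | 71.6% |

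None reaches 80%. The first row is the most favourable one that honours the stated drop-out.

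**What would bring the figure back**

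| Departure from the stated inputs | n per group | Power, normal |
|---|---|---|
| 0.3 entered as R² (variance 6.3; correlation √0.3 ≈ 0.55): 119.8 × 1.5125 / 0.75 | 241.5 | 79.7% |
| Drop-out shrinks the cluster size in the design effect, but n is not inflated: 155.7 × 1.5125 | 235.5 | 80.8% |
| Alpha 0.05, no baseline adjustment, no drop-out: 141.3 × 1.70 | 240.2 | 80.0% |

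A near match also arises if 0.3 is the correlation between baseline and follow-up. With SD of change 3, the variance at each visit (taken as equal) is 9 / (2 × 0.7) = 6.43, the residual variance is 6.43 × 0.91 = 5.85, and power is 82.8% (normal) or 79.2% (t).

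**The case against.** **The blinded evaluation can repair it.** It could: a correct recalculation at that point would expose the shortfall, and adaptation is allowed. But the adaptation is discretionary, and the evaluation looks at the SD, the correlation and the ICC. If all three come out as assumed, nothing in them signals a problem, and power stays at about 63–68%. For the same reason one should not go further and say that the evaluation starts from wrong parameter values. The planning values themselves are not shown to be wrong; what fails is the step from them to 480.

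**Multiple imputation keeps all 480 in the analysis.** Imputation does not restore the missing 12-month information, and the plan itself counts 25% drop-out as a loss. Complete data would also fall short, at 75.6%.

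**The exact power depends on conventions that the article does not fix.** This stands. The 63% figure assumes 30 cluster-level degrees of freedom, and the 58–62% figures assume a design effect at 15 per DH. The normal approximation, 67.5%, is the simplest single figure; the others show that changing the convention does not restore 80%.

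**A reader might infer that 0.3 was used as R².** The document does not support that as a finding. The R² route needs 241.5 per group, or 16.1 DHs, marginally more than 16. Applying drop-out to the cluster size but not to n gives 15.7 DHs, which rounds up to 16 and leaves every listed parameter value as printed. The cause cannot be told from the article.

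**A null result would be over-read.** This is only partly fair, because results are to be given as mean differences with 95% confidence intervals, which would show whether 1 unit is excluded. Type I error, the analysis model and the treatment estimate are not affected.

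**Conclusion.** The point holds. With every listed input taken as written, 16 DHs and 240 older adults per group give about 67% power for 1 ROAG unit by normal approximation and about 63% with t on 30 df. They give 58–62% if the design effect stays at 15 per DH, and at most 76% with no drop-out. Power of 80% is reached at about 1.14–1.19 units, with drop-out reducing both n and cluster size. The gap between 240 and about 314 enrolled per group is too large to be rounding.

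The result rests on the inputs printed in the article, equal cluster sizes, and 0.3 being the correlation between baseline and change, as the text says. It does not show that the trial must enrol more, or which input was mishandled. It shows that the stated 80% does not follow from the stated assumptions, which should be put right before recruitment starts (planned for September 2025 under Trial status).

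**What to change.** Re-run the calculation from the saved software inputs and restate the paragraph in one of two ways:

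- Keep the listed assumptions and give the power they deliver: about 63–68% for 1 unit, or 80% for about 1.15–1.2 units. Name the design-effect convention, the degrees of freedom and the way drop-out entered.
- If a different input or drop-out handling was really used, print that one, justify it, and show that it leads to 16 DHs per group. Should the input turn out to be a proportion of variance explained of 0.3, the paragraph would have to state a correlation of about 0.55 and support it.

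Use the corrected calculation when the blinded evaluation judges whether to adapt the sample size, so that the shortfall is visible even if the SD, correlation and ICC come out as planned.

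The cost is one paragraph in the protocol, a matching registry update, and a less favourable power statement. No extra enrolment is needed to make the statement true; whether to enlarge the trial is a separate decision for the sponsor.

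### The blinded sample size review draws its SD, correlation and ICC from 6-month data, while the primary endpoint and the sample size concern change to 12 months

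*Protocol article*

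**What the plan says.** The list of primary outcomes in Phase VI of the protocol article defines them as "change from baseline to 12 months follow-up", for ROAG and GOHAI. The Data analysis section repeats this: "The primary endpoints (change in ROAG and GOHAI from baseline to 12-month follow-up) will be tested at significance level" 2.5%, two-sided.

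The sample size in the same section serves that endpoint: "480 older adults (240 per group) will be included to demonstrate a clinically meaningful difference of 1 unit in ROAG at 80% power". Its inputs are an SD ("SD of change scores from baseline values = 3 since the older adults as a group are heterogeneous"), a baseline correlation and cluster size ("Weak to moderate correlation between baseline values and change scores = 0.3, m = 15 older adults per DH") and an ICC ("a weak intraclass correlation coefficient within clusters = 0.05, significance level" 0.025), with 25% drop-out. No visit is named for the SD, correlation or ICC. Twelve months is implied because the calculation powers a 12-month endpoint.

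The review of these three inputs is then fixed as follows: "A blinded evaluation of the SD, correlation, and intraclass coefficient will be conducted when 6-month follow-up data has been retrieved for 50% of the planned" participants. The sample size may be changed if that is judged necessary. The text does not say in which direction, or how 6-month values would inform the 12-month assumptions. The follow-up lists in Phase VI show that ROAG and GOHAI are measured at both 6 and 12 months.

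**The concern.** The review is meant to test whether the assumptions behind the 12-month comparison are holding, but at its trigger it observes mainly the 6-month change. For a score with stable variance σ² and baseline to follow-up correlation ρ, the SD of change is σ√(2(1 − ρ)). If ρ falls as the interval lengthens, this SD grows, so 6-month data would tend to understate the 12-month SD.

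Two consequences are possible. Because the wording does not rule out a reduction, a favourable 6-month reading could be used to shrink the trial. Or the review could judge the sample adequate when the 12-month SD is too large for it. In either case the primary comparison would have less power than the review reports.

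**Working it through.** **Inputs** (protocol article, Data analysis): difference δ = 1 ROAG unit; SD of change 3; correlation of baseline with change r = 0.3; ICC 0.05; 15 older adults per DH; 16 DHs per arm; two-sided α = 0.025; drop-out 25%. Completers per DH: 15 × 0.75 = 11.25. Completers per arm: 16 × 11.25 = 180. All power figures below use the normal approximation.

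**The plan's own figure.**
- Residual SD after baseline adjustment: 3 × √(1 − 0.3²) = 2.862.
- Per arm without clustering: 2 × (2.2414 + 0.8416)² × 2.862² / 1² = 155.7.
- Design effect on completers: 1 + (11.25 − 1) × 0.05 = 1.5125. Then 155.7 × 1.5125 / 0.75 = 314 per arm, or 314 / 15 = 20.9, so 21 DHs.
- Design effect with m = 15: 1 + 14 × 0.05 = 1.70. Then 155.7 × 1.70 / 0.75 = 353 per arm.
- The stated 240 per arm is not reproduced. With 180 completers the effective n is 180 / 1.5125 = 119.0 per arm, the standard error is 2.862 × √(2 / 119.0) = 0.371, and power is Φ(1 / 0.371 − 2.2414) = 67.5% (about 63% with a t test on 30 df).

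This shortfall involves no 6-month data. It is a separate question about the sample size and is not counted here as an effect of the review.

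**Isolating the effect of the visit.** Take the SD at which the fixed design has exactly 80% power. The standard error must be 1 / (2.2414 + 0.8416) = 0.3244. The residual SD is then 0.3244 / √(2 / 119.0) = 2.502, and the SD of change is 2.502 / √(1 − 0.3²) = 2.62. Suppose the review reads 2.62 at 6 months and leaves 480 unchanged. If the 12-month SD is k times as large, true power is Φ(3.0830 / k − 2.2414):

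| 12-month SD relative to the 6-month reading | True power |
|---|---|
| 10% smaller | 88% |
| equal | 80% |
| 5% larger | 76% |
| 10% larger | 71% |
| 20% larger | 63% |
| 30% larger | 55% |

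**The other two parameters**, with SD 2.62 at both visits:
- ICC at 12 months of 0.02, 0.08 or 0.10 instead of 0.05: power 89%, 72% or 66%.
- r of 0 or 0.5 instead of 0.3: power 76% or 88%.

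The multipliers and alternative values are assumptions chosen to show a range. The documents supply no ROAG SD, correlation or ICC specific to 6 or to 12 months.

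**The case against.** Using an earlier visit for a blinded size review is a normal, practical choice. ROAG is measured after baseline only at 6 and 12 months, and waiting for 12-month data on half the sample would leave little room to adapt, particularly as the Trial status section has recruitment starting in September 2025 and data collection ending in September 2026. A full re-estimation algorithm may also sit in the full protocol or analysis plan. All of this stands, so the timing should stay and the absence of an algorithm is not the point. What remains is that the article itself fixes the visit, the three parameters and an adaptation with no stated direction.

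A reader might go further and infer that the error runs in the unsafe direction and that the review would show a comfortable margin while true power is 68%. One route assumes equal variances over time and geometric decay of correlation. Then ρ at 12 months is 1 − 2 × 0.3² = 0.82 and σ is 3 / √(2 × 0.18) = 5. At 6 months ρ is √0.82 = 0.906, the SD of change is 2.17 and apparent power is about 92%. The documents do not support this as a finding, for four reasons:
- They give no values for either visit.
- Equal variances force the correlation of baseline with change to be negative, because the covariance is (ρ − 1)σ²; the article prints 0.3 with no sign.
- The ICC is held constant, although it is one of the reviewed parameters. With no decay between 6 and 12 months the two SDs agree.
- The 68% arises because 480 does not follow from the stated inputs. If 480 did give 80% power at 12 months, a low 6-month SD that left 480 in place would cost nothing.

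**Conclusion.** The point holds in a limited form. The review checks 12-month planning inputs on 6-month data. It can harm power in two ways: by supporting a cut, or by missing a shortfall such as a 12-month SD larger than the one it read. A larger 12-month SD is likely if correlation weakens with time and variances are stable, but the opposite is possible and would lead to unneeded recruitment instead. In size, a 12-month SD 10% to 20% above a reading of 2.62 lowers power from 80% to between 71% and 63%, while one 10% below raises it to 88%. These figures assume 16 DHs per arm, 11.25 completers each, ICC 0.05, r 0.3, two-sided α 0.025 and the normal approximation. That SD 3 refers to 12 months is inferred from the endpoint. This should be settled before recruitment starts, but it does not show that the review will mislead.

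**What to change.** Keep the 6-month trigger and add to the Data analysis section that:
- the blinded review may only maintain or increase the sample size, never reduce it;
- the SD used for the 12-month endpoint is the larger of the observed 6-month SD and the planned 3;
- any 12-month data already available at the review are also used.

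The cost is one or two sentences. The review can no longer justify a smaller trial, and if the 12-month SD is in fact below 3, the floor may prompt some recruitment that was not needed.

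The sample size calculation should be reconciled at the same time. With SD 3, r 0.3 and ICC 0.05 the formula above asks for 21 DHs per arm, so a review with this floor would call for an increase even if the data confirmed every planning assumption.
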